## Abstract

**Background:**

Healthcare facilities are notorious for occupational health and safety problems. Multi-level interventions are needed to address interacting exposures and their overlapping origins in work organization features. Worker participation in problem identification and resolution is essential. This study evaluates the CPH-NEW Healthy Workplace Participatory Program (HWPP), a *Total Worker Health*® protocol to develop effective employee teams for worker safety, health, and wellbeing.

**Methods:**

Six public sector, unionized healthcare facilities are enrolled, in three pairs, matched by agency. The unit of intervention is a workplace health and safety committee, adapted here to a joint labor-management “Design Team” (DT). The DT conducts root cause analyses, prioritizes problems, identifies feasible interventions in light of the constraints and needs of the specific setting, makes business-case presentations to facility leadership, and assists in evaluation.

Following a stepped-wedge (cross-over) design, one site in each pair is randomly assigned to “immediate intervention” status, receiving the full coached intervention at baseline; in the “lagged intervention” site, coaching begins about half-way through the study. Program effectiveness and cost-effectiveness outcomes are assessed at both organizational (e.g., workers’ compensation claim and absenteeism rates, perceived management support of safety) and individual levels (e.g., self-rated health, sleep quality, leisure-time exercise). Targeted pre-post analyses will also examine specific outcomes appropriate to the topics selected for intervention. Process evaluation outcomes include fidelity of the HWPP intervention, extent of individual DT member activity, expansion of committee scope to include employee well-being, program obstacles and opportunities in each setting, and sustainability (within the available time frame).

**Discussion:**

This study aims for a quantitative evaluation of the HWPP over a time period long enough to accomplish multiple intervention cycles in each facility. The design seeks to achieve comparable study engagement and data quality between groups. We will also assess whether the HWPP might be further improved to meet the needs of U.S. public sector healthcare institutions. Potential challenges include difficulty in pooling data across study sites if Design Teams select different intervention topics, and follow-up periods too short for change to be observed.

**Trial registration:**

ClinicalTrials.gov NCT04251429 (retrospectively registered January 29, 2020), protocol version 1.

## Background and rationale

### Occupational health and safety in the healthcare sector

Healthcare is one of the largest sectors in the U.S. economy, with over 16 million employees, representing 11% of the U.S. labor force [1]. Eighteen of the 30 fastest-growing professions in the U.S. are in healthcare and associated sectors; they are expected to create more than 3.4 million additional jobs by the year 2028 [2]. The largest projected increases are for home health professionals and personal care assistants [2, 3]. Other professions such as nurse practitioners, physician technicians, and medical assistants also represent steady demand as the healthcare sector shifts towards team-based services [3].

Numerous exposures in the healthcare work environment include excessive physical workload (e.g., patient handling), biological agents, cleaning and disinfection chemicals, shiftwork with extended hours, electronic data entry, assaults, and psychosocial stressors. Not all of the resulting health effects are recognized or reported as work-related. Nationally, the reported incidence rate of recordable non-fatal occupational injuries and illnesses for healthcare and social assistance jobs was 4.1 per 100 full-time workers in 2017 and 3.9 in 2018 [4].

The type and severity of injuries vary by job title. Compared to all occupations (private sector), psychiatric aides have among the highest incidence rates for non-fatal workplace injuries requiring days away from work (647.7 per 10,000 full time workers) [5]. Among other healthcare professions, orderlies and nursing assistants’ rates were 283.3 and 255.7, respectively [5]. Rates for registered nurses (RNs) were 88.4, licensed practical and vocational nurses (LPNs) 85.6, healthcare social workers 25.4, and mental health and substance abuse social workers 14.7 [5].

In 2018, incidence rates for nonfatal occupational injuries and illnesses resulting in days away from work among public sector (state government) healthcare occupations were considerably higher than those of their private sector counterparts [6]. Public sector psychiatric aides’ incidence rates were 1475.7 per 10,000 full time workers, nursing assistants 445.9, RNs 194.5, and LPNs 427.7 per 10,000 [7].

The most common events recorded for injuries with days away from work for psychiatric aides were related to violence [5]. In the U.S., violence from patients, visitors, and coworkers is often tolerated as inevitable in the healthcare workplace [8]. The U.S. Occupational Safety and Health Administration (OSHA) has issued prevention guidelines that include engineering controls for primary prevention [9]. However, the typical and often sole strategy offered for preventing health care worker injuries from assault is training in management of patient/client behavior; OSHA’s guidelines are often not implemented and occupational safety personnel are typically not engaged in problem analysis and solutions [10, 11].

Musculoskeletal disorders (MSDs) such as sprains, strains and tears are a common nature of injury among all healthcare workers [12]. For nursing assistants and RNs, overexertion and bodily reaction were the most common types of reported incidents [5]. In 2016, over 19,790 registered nurses in private industry sustained musculoskeletal injuries that resulted in lost work days [13]. In 2015, registered nurses and nursing assistants were two of the top six occupations for lost-workday MSD rates [14]. Nearly 20,000 nursing assistants and over 11,000 registered nurses sustained musculoskeletal injuries that resulted in missed days from work [14]. Other healthcare job groups with notable MSD risk include physical and occupational therapists [15], laboratory technicians [16], housekeeping [17], maintenance workers, laundry, and food service workers [18].

Patient handling is recognized as a major cause of MSDs for clinical staff [19]. For direct care personnel, patient/resident lifting devices can reduce biomechanical load and injury risk [20–24]. However, many facilities do not have sufficient equipment; patient needs and limited co-worker availability for assistance can challenge a structured lifting program. Biomechanical considerations may be complicated by other job features, such as time pressure, staff-supervisor interaction, combative patients [24], and attention to infectious disease risk [25]. Potential effect modification of lifting demands by personal factors such as obesity, cigarette smoking, or depression is still understudied [26]. Further, patient handling is not the only ergonomic demand in caregiving jobs, which also involve lifting of material loads, bending and twisting, and standing for long periods of time.

Job stress and burnout are high among healthcare workers and associated with both psychological and somatic distress [27–29]. Psychosocial stressors, night work, and workplace assault are associated with chronic disease risk factors such as smoking, physical inactivity, obesity, sleep, and mental wellbeing [30–32], health concerns that are not typically attributed to work. Psychosocial stressors have also been linked to high staff turnover intention in nursing homes [32]. Healthcare institutions face substantial challenges in retaining direct care personnel due to workplace health and safety issues. Annual turnover rates for registered nurses are estimated to range from 18 to 26% [33], with cost estimates for each turnover ranging from $62,100–$67,000 [34]. High personnel turnover impacts organizational conditions that increase workplace hazards, creating a vicious cycle and posing challenges for patient safety and quality of care.

This multiplicity of hazards and outcomes poses practical challenges for employee health champions. It can be difficult to prioritize efforts, especially when there is insufficient understanding about how exposures interact with each other, how to interrupt the positive feedback loops, and whether there are common barriers to improving working conditions in these various domains. There is an emerging agreement that workplace health interventions should operate at multiple levels of influence [35], and that health and safety interventions should address work organization and empowering employees in problem identification and resolution [36, 37]. However, there is limited experience with a systematic approach to identify and address the interplay among this myriad of causal factors in order to improve healthcare worker mental and physical health effectively [29, 38, 39].

### Total Worker Health®

The U.S. National Institute for Occupational Safety and Health supports a *Total Worker Health*® (TWH) research program to examine the combined effects of workplace and non-workplace factors on worker safety, health and well-being [40, 41] and to evaluate trials of integrated workplace efforts. Evaluation literature is sparse to date and TWH approaches and goals vary among investigators [42–44].

One strategy to elucidate the relevant occupational and non-occupational risk factors, and how they interact, is participatory action research [45]. In a participatory approach, employees are actively engaged in problem identification and prioritization, decision-making, implementation, and evaluation of the program. This supports effective program implementation and uptake because employees are well qualified to identify opportunities and obstacles present in their work environment [44, 46]. Key features include collaboration, mutual education, and acting on results developed from research questions that are relevant to the community [47, 48]. Previous studies have demonstrated the importance of direct involvement of employees and their levels of influences in the process of program implementation [49, 50]. Decision latitude is itself a key psychosocial determinant of worker health. Thus, providing opportunities for workers to identify problems, set priorities, and design and assess health and safety programs should contribute to improving worker health both directly and indirectly [51].

The Healthy Workplace Participatory Program (HWPP) (http://www.uml.edu/Research/Centers/CPH-NEW/Healthy-Work-Participatory-Program/) is an innovative, evidence-based protocol to facilitate worker participation in priority-setting, root cause analysis, and development, implementation, and evaluation of integrated solutions to workforce health problems. It promotes employee empowerment and engagement to address a wide range of work environment, work organization, and safety and health issues through organization-level change. New understandings emerge as participants reflect on interventions in light of their first-hand knowledge. Preliminary evaluations have shown high user acceptance and positive process outcomes [44, 52, 53].

### Objective

This study, Safety and Health through Integrated, Facilitated Teams (SHIFT), undertakes a prospective evaluation of the HWPP in the healthcare sector. The overall goal is to increase effectiveness of health and safety committees to undertake root cause analysis, problem-solving, and development of solutions. The study will generate quantitative and qualitative evidence regarding its feasibility and effectiveness as a process for obtaining integrated solutions to challenges for worker health. The primary short-term hypothesis is that the health and safety committees will become more active and engaged. Longer-term goals are that the committees become more effective in implementing measures to improve workforce health and safety. Because all study sites come from the same economic sector, generalizable knowledge may be derived regarding the needs and challenges of public sector healthcare facilities. The findings may also identify needs for any further revisions to the HWPP toolkit.

## Methods

### Setting and population

The study is carried out in six public sector healthcare facilities, one pair from each of three agencies. Four of these are run by the state of Massachusetts Executive Office of Health and Human Services: two Department of Mental Health hospitals and two residential facilities for veterans. The other two are inpatient/outpatient facilities of the U.S. Veterans’ Administration.

These agencies all have pre-existing workforce safety and health infrastructure. The Veterans’ Administration has multiple initiatives addressing employee health and safety on a national scope and has been particularly recognized for the excellence of its safe patient handling program [54, 55]. Various committees address Environment of Care, accident review, safe patient handling, violence prevention, and in some facilities health promotion.

In Massachusetts, every executive-level branch of state government is required to have a Safety and Health Coordinator and joint labor-management health and safety committees [56]. State law also mandates that all state agencies provide employees with safety and health protections at least as protective as federal OSHA requirements. Health and Human Services has been one of the most pro-active state agencies, creating an occupational health and safety infrastructure with committees in every agency and assigning a secretariat-level coordinator. Regional workers’ compensation managers review claims data with the coordinator on a regular basis.

Individual study sites were recruited according to the following criteria:
Active, high-level interest in a participatory, integrated occupational health program.An existing occupational health and safety committee with front-line staff members that meets regularly, has a designated facilitator or chair, and is willing to consider expansion of scope to include worker well-being.Openness to high degree of worker participation in development and implementation of solutions.Leadership recognition and acceptance of the necessary in-kind personnel time commitment (manage survey logistics, coordinate transmission of administrative data files); openness to broadening the scope of issues over time; and willingness to be oriented to the designed management role.

### Study design

The study has a stepped-wedge design [57], meaning a prospective study with concurrent controls that later cross over to intervention (Fig. 1). Study sites are enrolled in matched pairs. Within each pair, one facility is randomly assigned to “immediate intervention” status and receives the intervention as early as possible during the project period, following baseline data collection. The research team provides coaching to co-facilitators and champions throughout the implementation process, in order to enhance fidelity, engagement, and effectiveness. The other facility, designated as the “lagged intervention” site, has status-quo control group status for the first half of the project, continuing with the safety process already in place at that facility until mid-way through the timeline. At that point, the three immediate intervention sites will continue with the HWPP process independently, and the HWPP coaching will be transferred to the lagged intervention sites.

**Fig. 1 Fig1:**
[figure not shown]
Study timeline for the SHIFT project, with key elements of the stepped-wedge design

The lag period seeks to obtain adequate observation time with concurrent controls for the intervention sites, as well as follow-up time to examine the interventions that the control sites undertake before the end of the study. During the lag period, all sites have access to health and safety information upon request from the researchers, on topics prioritized by committee members (e.g., ergonomics/safe patient handling; assault prevention; shift work and sleep quality; job stress prevention).

At the time of randomization, findings are presented to the facility Steering Committee (SC) and the Design Team (DT) co-facilitators from the baseline formative assessments (below) of key challenges to employee health, safety, and wellbeing, as well as opportunities and barriers for the participatory process. Similarly, throughout the project the researchers will report key descriptive findings from administrative data and employee surveys (see below) to the DT’s and SC’s for their use in priority-setting.

### Intervention protocol

The HWPP intervention is delivered at the institutional level. A coach from the research team assists each facility to implement the CPH-NEW Intervention Design and Analysis Scorecard (IDEAS) process [53]. The steps in the HWPP program are described and illustrated with training videos and example worksheets on the CPH-NEW website (www.uml.edu/cphnewtoolkit/IDEAS).

The key working group is the Design Team. Because each participating healthcare facility had at least one existing joint management-labor health and safety team, most typically an Environment of Care committee, the HWPP has been adapted to this membership structure. During the recruitment and start-up period, specific instructions are provided regarding equal numbers of DT members from the rank-and-file workforce and management, and avoidance of direct supervisory relationships between any pair of DT members. The researchers expended substantial time in pre-study communication with facility leadership as well as the multiple bargaining units at each site to ensure clear understanding of these ground rules and selection of representatives enthusiastic to participate. Two employees per site were trained as co-facilitators, one from labor and one from management. Besides seeking balance in perspectives, having co-facilitators seeks to ensure continuity in case of employee turnover and to set the stage for longer-term sustainability.

Within each facility, the existing management decision-making group is designated the HWPP Steering Committee and a senior manager plays the role of program “champion.” The champion attends the initial trainings, participates in quarterly study oversight meetings, and agrees to maintain regular communication with the DT co-facilitators. A structured process defines the sequence of activities and key communications between the DT and SC, which provides the DT with constructive feedback about the proposals, selects interventions to be implemented, and provides any needed resources for refining, implementing, and evaluating interventions.

The researchers orient all DT members and the champion to the study design, the HWPP, and the study roles. Additional training is provided as the DT moves through the stages of the HWPP: meeting management skills (agendas, minutes, tracking action items); use of fishbone diagrams to identify root causes of selected safety/health concerns; development of solutions through systems analysis; strategies for presenting these to the facility leadership team; and techniques to evaluate DT activities and use these results to guide refinements and related solutions. Finally, the teams will present these ideas to leadership, creating effective and meaningful dialogue.

Because interventions are designed through a participatory process, the DT and SC members at each site – not the researchers – select the intervention goals and activities to be carried out. Based on prior experience in the healthcare sector, review of earlier workers’ compensation claims from these three agencies, and conversations during the recruitment process, key issues likely to be selected at the participating facilities include psychosocial job stress and burnout; verbal and physical assault; physical ergonomics (including but not limited to patient handling); overtime, shiftwork, and sleep quality; and traditional safety issues (e.g., slips, trips and falls). In accordance with the Total Worker Health mission, the DT’s are specifically invited to consider interactions between the work environment and personal well-being/health behaviors (exercise, nutrition, sleep, etc.), and whether these might have shared or overlapping solutions.

The researchers anticipate at least one issue to be selected and intervened on per year at each site, once active coaching begins. By the mid-point of the study, each immediate intervention DT should have completed at least two complete IDEAS cycles and be prepared to continue the process more independently. The coach will reduce active assistance while maintaining contact through regular telephone or e-mail check-ins with DT members and co-facilitators to assess progress, learn about problems or concerns, and offer advice if requested. Research staff will continue to be available as a technical resource when DTs take up new topics.

### Evaluation

The program implementation process and effectiveness will be evaluated, using qualitative and quantitative methods, at the levels of the institution, program team members, and individuals affected by interventions generated by the teams (Table 1). A program logic model of the HWPP outputs and outcomes guides the selection, development and use of the evaluation elements (Fig. 2), informed by that of Strickland et al. [58]. This section describes process evaluation measures to evaluate HWPP outputs, and formative and effectiveness evaluation measures to describe HWPP outcomes.

**Table 1 Tab1:** Qualitative and quantitative instruments for process, formative, and effectiveness evaluation in the SHIFT project

Instrument	Description	Content	Administration Frequency
**Process Evaluation**			
*Mobile App, “HWPP Assistant”*	Meeting assessments and time logs by DT and SC members	• DT members and co-facilitators: participation^a^, knowledge, satisfaction, team effectiveness, engagement^a^, value • DT co-facilitators: confidence in facilitating; quality and usability of HWPP materials • SC members: awareness of team developments, organizational disturbances, team effectiveness, value, engagement • Log of project-related time (level of participation^a^)	After each meeting
*Coach Notes; Research Assistant Notes*	Systematic, qualitative observations of DT, SC, and joint DT/SC meetings	• Attendance^a^ • Team dynamics^a^ • Quality of Design Team facilitation (DT only) • Level of management support (DT only) • Progress through the structured IDEAS intervention design process^a^ • Any difficulties with the IDEAS process; any adaptations made	After each meeting
*Design Team Meeting Records*	Person-time invested; Fidelity of DT meetings to HWPP protocol	• DT meeting dates^a^ • Time spent in meetings^a^ • Number of attendees^a^ • Agenda items covered from the protocol	After each meeting
**Formative and Effectiveness Evaluation: Short and Medium-term Outcomes**			
*IDEAS Worksheets*	DT work record of progress on IDEAS steps (summary worksheet)	• Content of discussions and interventions at each step: knowledge, breadth of topics covered over time^a^	After IDEAS Step 5
*Process Check-up*	DT and SC members: periodic survey evaluating the HWPP	• Organizational support and engagement^a^ • DT and SC engagement^a^ • Program facilitation • Intervention planning/implementation	After IDEAS Step 5, then every 6 months during coaching
*Design Team Survey*	DT survey on members’ attitudes and perceptions of HWPP	• Member engagement^a^; Involvement^a^ • Managerial support for DT interventions • Shared DT/SC knowledge and understanding about root causes of safety and health concerns • Quality of organizational communication • Expected HWPP impact • Any unplanned consequences observed (negative or positive)	After IDEAS Step 5, then every 6 months during coaching
*Interim Champion & Facilitator Interviews*	Semi-structured interviews for champions and co-facilitators	• Satisfaction regarding program implementation • Quality of and trends in DT and SC effectiveness, engagement^a^, involvement^a^, communication and organizational support • Expectations regarding impacts of the participatory program overall and from the interventions being designed and implemented by the teams	Every 6 months during coaching

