#### Process evaluation

The HWPP relies on continuous participatory engagement of program participants and the workforce so that the workers’ own knowledge can inform customization of the program to local conditions, in keeping with the principles of participatory action research. Thus, a substantial amount of planned evaluation addresses the implementation process and corresponds to the Logic Model elements of “Activities and Outputs.”

Process evaluation addresses potential generalizability of the results by documenting specific conditions that necessitate customization as well as quantifying personnel and other resources needed for implementation. The choice of process measures is informed by implementation science research frameworks [59–61] with adaptations for the occupational safety and health setting [62]. For example, the level of participants’ engagement, enthusiasm and confidence in their roles is expected to predict the success of the program. Quality and usability of the program materials are also likely predictors. Characteristics of the implementation process include the participants’ efforts in planning, engaging, executing, reflecting, and evaluating the program steps. External forces and organizational characteristics of the study sites may either facilitate or impede program implementation.

Process measures registered as *primary outcomes for this clinical trial* are team attendance, team engagement, level of committee activity, and scope of health, safety, and well-being issues addressed. Process measures registered as *secondary outcomes* include proportion of the HWPP protocol and content followed (fidelity), and development of shared labor-management awareness of job-related health issues.

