### Data analysis

#### Process evaluation

Short-term process measures will be summarized for each committee over time and compared between the control and intervention groups. For example, changes in implementation metrics will quantify the extent to which the participatory DTs utilized the HWPP program (uptake) and adhered to it (fidelity, sustainability). The DT surveys and Coach notes will be summarized to document the development of team functionality, independence, ability to plan and implement activities, and ability to evaluate success or setbacks of activities to improve the process in the future. We will also describe obstacles and opportunities in each setting, and the extent to which these are similar among agencies.

We will summarize the accomplishments of the HWPP and the factors observed to affect implementation and outcomes of the program; the challenges and successes of long-term team maintenance; and how these were different from or similar to the challenges and successes of the health and safety committees in the control sites before the lagged interventions. We will discuss the implications of these combined qualitative and quantitative findings for potential long-term sustainability of the participatory programs. These findings may be relevant to post-hoc analyses of any site differences in effectiveness and will also inform future refinements in HWPP content or delivery.

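### Scope of issues and survey- or interview-based engagement, both flagged primary, are collected only after IDEAS Step 5 or during coaching, so they have no control-phase or pre-intervention value

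*Protocol article*

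**What the plan says.** The Objective section states a hypothesis of change: "the health and safety committees will become more active and engaged". Under Evaluation, Process evaluation, the registered primary outcomes are "team attendance, team engagement, level of committee activity, and scope of health, safety, and well-being issues addressed"; fidelity to the HWPP is registered as secondary. Under Data analysis, Process evaluation, the plan is that "Short-term process measures will be summarized for each committee over time and compared between the control and intervention groups", with a further contrast against the control-site committees before they cross over.

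Table 1 marks the primary items and gives each instrument a schedule. In its short- and medium-term block:

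- The Process Check-up and the Design Team Survey, both flagged for engagement, run "After IDEAS Step 5, then every 6 months during coaching".
- The Interim Champion & Facilitator Interviews, flagged for engagement and involvement, run six-monthly while coaching lasts.
- The IDEAS Worksheets, completed after Step 5, carry the flagged item "breadth of topics covered over time^a".

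The process block of the same table flags "Progress through the structured IDEAS intervention design process" as primary.

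Under Study design, a lagged site keeps its existing safety arrangements until about the midpoint. Under Study revisions after the start date, about 1.5 years of concurrent comparison remain.

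**The concern.** A hypothesis that committees become more active and engaged needs a starting value, a concurrent control value, or both. An instrument triggered by an IDEAS step or by coaching supplies neither: a control committee never reaches the trigger, and an intervention committee reaches it only once the program is under way. Lagged sites do contribute later, but only after crossover.

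At stake are two of the four registered primary outcomes, scope and engagement. On the affected instruments the study would have only levels in coached teams. Yet the Effectiveness evaluation part of Data analysis says that improvements in worker engagement will be read as evidence that the participatory process works.

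The flag on IDEAS progress is a related problem. A committee that has not been given the IDEAS process has no progress to record, so a between-group comparison on that item favours the intervention by definition.

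**Working it through.** The plan gives no figure to reproduce here. The check sets each flagged row of Table 1 against the control condition described under Study design.

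| Table 1 row | Flags | Schedule | Control-phase value at lagged sites | Pre-intervention value |
|---|---|---|---|---|
| Mobile app | 3 | every meeting | possible, not stated | possible, not stated |
| Coach / research assistant notes | 3 | every meeting | possible, not stated | possible, not stated |
| Design Team meeting records | 3 | every meeting | possible, not stated | possible, not stated |
| IDEAS Worksheets | 1 | after Step 5 | none | none |
| Process Check-up | 2 | after Step 5, then six-monthly while coached | none | none |
| Design Team Survey | 2 | after Step 5, then six-monthly while coached | none | none |
| Interim interviews | 2 | six-monthly while coached | none | none |
| Leadership Interviews | 1 | baseline and study end | baseline only; study end falls after crossover | yes |

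**Counts.** Flags: 3 + 3 + 3 + 1 + 2 + 2 + 2 + 1 = 17, in 8 rows. Rows tied to Step 5, coaching or both: 4 of 8, which is every row of the short- and medium-term block. They hold 1 + 2 + 2 + 2 = 7 of the 17 flags.

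**By registered primary outcome.**

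- *Scope of issues.* One flagged source, the IDEAS Worksheets. It has no control-phase value and no baseline.
- *Engagement.* Four rows flag it by name: the app, the Process Check-up, the Design Team Survey and the interim interviews. Three of the four are tied to coaching or Step 5, which leaves the app.
- *Attendance and committee activity.* Attendance, meeting dates, time spent and participation come from the three rows completed at every meeting. No Step 5 or coaching condition is attached.

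**Waves in the comparison window.** Number of six-monthly waves = window / interval = 1.5 / 0.5 = 3. As scheduled, the two surveys and the interim interviews give 0 waves in control committees, at most about 3 in immediate-intervention committees, and no baseline in either. On a common calendar, each committee would give 1 baseline plus about 3 waves.

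**Internal consistency.** The Effectiveness evaluation part of the Evaluation section describes a semi-annual survey of Design Team members with no Step 5 or coaching condition. Table 1 attaches both. The two need reconciling.

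**The case against.** The strongest reply is that the promised comparison concerns short-term process measures, and Table 1's process block is the one completed at every meeting. The restricted rows sit under a different heading, and the Data analysis section says only that Design Team surveys will be summarized. This ambiguity is real. It does not settle the matter, because the Evaluation section itself lists scope and engagement among the process measures registered as primary, and scope has no flagged source in the process block.

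Second, the Design Team is the existing committee in adapted form, two co-facilitators were trained at each site, and baseline findings go to co-facilitators at randomization. The meeting instruments may therefore run at lagged sites throughout, and a condensed article could leave that to the full protocol. This stands as a possibility. But the rows are framed around Design Team meetings, a coach and the HWPP, so it is not assured.

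Third, IDEAS progress can be read as committee activity, not fidelity, so its flag is not a flat contradiction of the registered list. That is fair. It still cannot serve as a between-group outcome when control committees score zero by construction.

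Fourth, much of the Design Team Survey asks about the HWPP and cannot be put to a committee that has not met it. This is correct, and it limits the remedy to generic items.

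A reader might infer that control committees yield no comparable data on any primary outcome, that no baseline exists at all, or that IDEAS progress is the only item left to compare. The documents do not support this. Attendance, meeting dates, meeting time, participation and app engagement carry no coaching restriction, and Leadership Interviews record employee involvement at baseline. Nor does all collection end with coaching: that limit applies to the Process Check-up, the Design Team Survey and the interim interviews.

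**Conclusion.** The point holds for the four short- and medium-term rows, which are 4 of the 8 rows flagged primary. As scheduled, they give zero observations from lagged sites in the roughly 1.5-year control window and no pre-intervention value at any site. Scope of issues is the most exposed, because it has no other flagged source. Engagement loses three of its four flagged sources for the comparison and rests on the app. Attendance and committee activity are sound if the after-meeting records are kept in control committees during the lag.

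This rests on two assumptions: that Table 1 is followed literally, and that lagged committees do not work through IDEAS steps before coaching begins, as Study design implies. If the full protocol follows the unrestricted semi-annual schedule and surveys committees at every site from baseline, the gap in the Design Team Survey closes. The scope gap remains.

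**What to change.** 1. Code scope of issues from committee minutes at all sites, for the same calendar periods, starting at baseline. The HWPP trains teams in minute-taking, so use a coding scheme that does not reward fuller minutes.
2. Give the generic engagement and involvement items of the Design Team Survey, not the HWPP-specific ones, to committee members at every site at baseline and every six months, regardless of coaching. Reconcile Table 1 with the semi-annual schedule in the Effectiveness evaluation section.
3. State that the after-meeting records are also kept in control committees during the lag.
4. Report IDEAS progress as fidelity, not as a primary between-group outcome.
5. Where baseline or control-phase survey data can no longer be collected, restrict the control-versus-intervention comparison to outcomes measured in both groups, and report the coached-only instruments descriptively.

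The cost is a short questionnaire for small committees and abstraction of existing minutes. The downside is slight measurement contact with control committees. Minutes can be abstracted later if they exist; missed control-phase survey waves cannot be recovered.
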